### 2.2. Study Setting

The study is decentralized and fully remote. A single coordinating center will oversee recruitment, randomization, intervention delivery, data management, and safety monitoring. No in-person visits will be required. 

The study team comprises two senior physiotherapists and certified yoga instructors with more than 10 years of experience in therapeutic yoga, one physiotherapist with over 5 years of experience in therapeutic exercise for chronic fatigue and complex pain, three researchers responsible for online assessments, and one statistician in charge of data analysis. To ensure consistency across evaluations and intervention delivery, preparatory training sessions will be conducted prior to recruitment.

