### 2.7. Sample Size

Sample size estimation considered three study groups, a one-tailed test (a larger effect size is expected in the MBE group), an α value of 0.05, a type II error (β) of 0.20 (80% power), and a precision of 6 (equivalent to a 15% change in the primary outcome, CFQ-14 total score at 12 weeks). Fatigue variance was set at 56.5 based on a previous study with a comparable population, intervention, and measurement tools [41]. Allowing for a 20% dropout rate and a design effect of 2 (due to non-probabilistic convenience sampling), a total of 147 participants (49 per group) will be required. Calculations were made using software developed by the Clinical Epidemiology and Biostatistics Unit of the Complexo Hospitalario Universitario de A Coruña, Spain [42].

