### 2.10. Interventions

Two active, therapist-guided telerehabilitation protocols will be combined with education and compared with usual care: (a) an MBE program, and (b) a low-intensity aerobic and strength training program. Usual care will reflect routine medical management. All sessions will be delivered live Via Microsoft Teams, with groups of ≤7–8 participants, once weekly for 12 consecutive weeks, consistent with previous research in ME/CFS and PCS [29,43]. Each session will last 45 min, increasing by 5 min each month. Exercises will require only a chair, with both seated and standing options available. Adjustments based on physical performance and perceived fatigue or dyspnea will follow pacing principles to minimize PEM risk. Therapists will guide participants using in-session ratings of perceived exertion (2–3/10) and simple cues to maintain a safe and comfortable exercise practice. Participants may also pause or re-join sessions as needed and will be encouraged to practice regularly using recorded materials. Attendance to ≥70% of the 12 scheduled sessions will be considered adequate exposure. A session will be considered attended if the participant joins the live class and takes part at least partially (≥15 min or completion of ≥1 exercise block), in line with pacing allowances. Attendance will be tracked Via Microsoft Teams and verified by therapist logs.

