### 2.14. Statistical Methods

Statistical analyses will be conducted using IBM SPSS Statistics, version 26.0 (IBM Corp., Armonk, NY, USA), under an intention-to-treat framework. A complementary per-protocol analysis will include participants achieving ≥ 70% adherence. Baseline characteristics will be summarized as mean (standard deviation) or median (interquartile range, Q1–Q3) for continuous variables, and as frequencies (%) for categorical variables. Between-group comparability at baseline will be examined using chi-square or Fisher’s exact tests for categorical variables, and one-way analysis of variance (ANOVA) or Kruskal–Wallis tests for continuous variables, according to distributional assumptions. Normality will be assessed with the Shapiro–Wilk test and by visual inspection of histograms and Q–Q plots to identify skewness, kurtosis, or outliers. When appropriate, homogeneity of variances will be verified with Levene’s test.

The primary outcome (CFQ-14 total score at 12 weeks, post-intervention) will be analyzed using linear mixed-effects models (LMMs) with fixed effects for group, time, and their interaction (group × time), and random intercepts to account for within-subject correlation. This approach accommodates repeated measures and missing data under a missing-at-random assumption [55]. Estimated marginal means with 95% confidence intervals (CIs) will be reported. Effect sizes will be presented as standardized mean differences (Cohen’s d) and partial eta squared (η^2^).

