Secondary continuous outcomes (e.g., HRV, functional performance, pain, anxiety and depression, quality of life) will be analyzed using the same LMM framework. Model assumptions will be verified through residual diagnostics; if violations are detected, data transformations will be considered, or generalized LMMs with appropriate distributions (e.g., Poisson, gamma, binomial) will be applied. For categorical outcomes, between-group differences will be tested with chi-square or Fisher’s exact tests. Where adjustment for covariates is warranted (e.g., age, sex, baseline fatigue severity), logistic regression analysis will be performed, and odds ratios with their 95% CIs will be reported. No multiplicity adjustment will be applied to secondary outcomes, following common clinical trial reporting standards [56]. Pairwise post-hoc comparisons between groups and across time points will use Bonferroni correction for multiple testing. Unless otherwise specified, all tests will be two-tailed, with statistical significance set at *p* < 0.05, and results will include effect sizes and 95% CIs.

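### The design effect of 2 is given a reason that does not apply to a randomised comparison, and the primary model omits the live classes that could cause clustering

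*Protocol article*

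**What the plan says.** The sample size in 2.7 rests on "a one-tailed test (a larger effect size is expected in the MBE group"). Its further inputs are a 5% significance level, 80% power, a difference of 6 points on the 14-item Chalder Fatigue Questionnaire (CFQ-14) and a variance of 56.5. It then applies 20% dropout and "a design effect of 2 (due to non-probabilistic convenience sampling), a total of 147 participants (49 per group) will be required".

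Section 2.8 randomises individuals 1:1:1 in three waves, with 16–17 per arm per wave. Section 2.10 delivers both active programmes live, "with groups of ≤7–8 participants, once weekly for 12 consecutive weeks". Usual care (2.10.3) has no classes. The primary aim in the Introduction is MBE against low-intensity exercise, so both arms of the main contrast are taught in classes.

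The primary model in 2.14 has fixed effects for group, time and their interaction, and "random intercepts to account for within-subject correlation". The article names no class or therapist term, gives no ICC, and nowhere links the design effect to the classes.

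**The concern.** A design effect for sampling corrects the variance of a population estimate when the sample is not a simple random one. This trial estimates a difference between randomised arms. How volunteers came forward decides to whom the result applies, not how variable that difference is. The reason given for doubling the sample is therefore invalid.

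People who share a therapist and a class for 12 weeks may, however, end up more alike than people who do not. If so, outcomes within a class are positively correlated, and a model that treats classmates as independent overstates the information in the data. A participant-level intercept does not help, because it links one person's visits to each other and not the outcomes of different people. At stake are the confidence interval and p-value of the primary contrast, and a sample-size statement whose justification does not match the design.

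**Working it through.** **1. Reproducing 147.** Inputs from 2.7: variance 56.5 (SD √56.5 = 7.52), difference 6, one-tailed 5% (z = 1.645), 80% power (z = 0.842), dropout 20%, design effect (DE) 2.

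- n per arm = 2 × 56.5 × (1.645 + 0.842)² / 6² = 19.41
- with the design effect: 19.41 × 2 = 38.81
- with dropout: 38.81 / 0.80 = 48.52, rounded up to 49; 3 × 49 = 147. The stated figure reproduces exactly.
- without the design effect: 19.41 / 0.80 = 24.26, rounded up to 25; 3 × 25 = 75.

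**2. Number of classes.** An arm of 49 is made up of waves of 17, 16 and 16. With at most 8 per class that needs 3 + 2 + 2 = 7 classes; with at most 7 it needs 3 + 3 + 3 = 9. After 20% dropout, 49 × 0.80 ≈ 39 are evaluable, or m = 39/7 = 5.57 to 39/9 = 4.33 per class.

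**3. Effect of ignoring class on MBE versus exercise.** The ICC is an assumption. It is taken as the class share of the variance of the analysed 12-week outcome. DE = 1 + (m − 1) × ICC. The naive standard error is 1/√DE of its true value, and the real type I error of a nominal two-sided 5% test is 2 × [1 − Φ(1.96/√DE)].

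| ICC | DE (7 / 9 classes) | Naive SE ÷ true SE | Type I error |
|---|---|---|---|
| 0.01 | 1.05 / 1.03 | 0.98 / 0.98 | 5.5% / 5.4% |
| 0.02 | 1.09 / 1.07 | 0.96 / 0.97 | 6.1% / 5.8% |
| 0.05 | 1.23 / 1.17 | 0.90 / 0.93 | 7.7% / 7.0% |
| 0.10 | 1.46 / 1.33 | 0.83 / 0.87 | 10.4% / 9.0% |

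A simulation of a t-test that ignores class (40,000 null trials per setting, 39 per arm) gave 5.4% / 5.4%, 6.2% / 5.8%, 7.9% / 7.1% and 10.5% / 9.2%. At ICC 0 it gave 5.1% / 5.1%.

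For an active arm against usual care only one side is clustered, so the inflation is (DE + 1)/2. At ICC 0.10 this is 1.23 / 1.17, with a type I error of about 7.7% / 7.0%.

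**4. What 147 can absorb.** With 39 evaluable per arm, SE = 7.52 × √(2/39) × √DE = 1.70 × √DE. One-tailed power is Φ(6/SE − 1.645).

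- DE 1: 97%
- DE 1.33 to 1.46 (ICC 0.10): 92% to 90%
- DE 2: 80%, as planned

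These powers use the normal approximation and ignore the loss of degrees of freedom. DE 2 corresponds to ICC = 1/(m − 1): 0.17 for m = 7, 0.14 for m = 8, 0.22 for m = 5.57 and 0.30 for m = 4.33.

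**The case against.** The strongest reply is that the harm is conditional. Participants are individually randomised, so classmates share nothing before treatment. Delivery is remote, self-paced and individually adjusted, and the Discussion itself expects less peer interaction than in person. A small ICC is plausible, and at zero the planned model is unbiased in its standard errors. This stands: the documents fix the direction for any positive ICC, not the size.

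It can also be said that a separate analysis plan might contain a class term. That is possible, but 2.14 states both the random effect and its purpose, and class is not part of either. If such a term exists elsewhere, the two texts need reconciling.

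Three stronger readings are tempting and not supported.

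- A reader might infer that the trial is underpowered. On the plan's own one-tailed basis a design effect of 2 leaves 80% power. A figure of about 70% appears only on changing to a two-sided test. That conflict, between the one-tailed sample size and the statement in 2.14 that "all tests will be two-tailed, with statistical significance set at" p < 0.05, is a separate matter.
- A reader might infer that the factor of 2 was really meant for the classes. The article gives a different reason, and none should be supplied in retrospect.
- A reader might infer from the staffing in 2.2 ("two senior physiotherapists and certified yoga instructors with more than 10 years of experience in therapeutic yoga", plus one physiotherapist for therapeutic exercise) that therapist is wholly confounded with programme. That section does not assign therapists to arms.

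**Conclusion.** Two points hold. First, the reason given for the design effect is wrong, and the factor nearly doubles the sample (75 to 147). Second, the primary model as written has no place for class, although both arms of the primary contrast are taught in classes. For any positive ICC its interval is too narrow and its p-value too small. Under assumed ICCs of 0.01 to 0.10, with 39 evaluable per arm in 7–9 classes, the standard error is about 2% to 17% too small and the type I error about 5.4% to 11% instead of 5%.

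It would go too far to say that the standard errors are too small as a matter of fact, since no ICC is given. It would also go too far to call the sample inadequate: 147 covers an ICC of about 0.14–0.17 with 7–8 evaluable per class, and more with smaller classes. The damage is to the inference and to the accuracy of the sample-size statement.

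**What to change.** **In 2.7:** withdraw the convenience-sampling reason and keep 147. State an assumed class size and ICC range with the resulting power, presented as the clustering that the sample can absorb and not as the basis on which it was chosen.

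**In 2.14:** add a class random effect in the two active arms only, with none for usual care (a partially nested model). It should act at the post-baseline visits. Classes share no treatment effect at baseline, and a class intercept constant over time would cancel from the change contrasts and leave the problem in place. Specify small-sample degrees of freedom (for example Satterthwaite), state a fallback if the class variance is estimated at zero, and report the class ICC.

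**Data:** record a class identifier for each active-arm participant. Section 2.10 already tracks attendance through Teams and therapist logs, but does not say that class is stored. Because 2.9 keeps the analyst blinded, supply the identifier in coded form, for example with single-member dummy codes for usual care. This limits unblinding but may not prevent it, since the pattern can still give usual care away; the two active arms can stay masked from each other.

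**Cost:** slightly wider intervals and fewer degrees of freedom (about 12 to 16 for the primary contrast, from 7 to 9 classes per arm). No extra participants or visits are needed. The change should be made before unblinding, so that the model is not chosen after the result is known.

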### 2.8. Allocation to Interventions

Eligible participants will be randomly assigned to one of three arms: (1) MBE, (2) conventional low-intensity exercise, or (3) usual care. Recruitment will occur in three waves (*n* = 50, 49, and 48), each randomized independently to ensure a 1:1:1 ratio (16–17 participants per arm per wave). Randomization sequences will be computer-generated in R (with seed set for reproducibility) using stratified lists to minimize imbalance across groups. The R script for the stratified randomization is in Supplementary File S1. Allocation concealment will be ensured with sequentially numbered, opaque, sealed envelopes, prepared by an independent collaborator not involved in recruitment or assessment. Envelopes will be opened only after consent and completion of baseline assessments.

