#### Additional Analyses

Exploratory analyses will examine potential moderators and predictors of treatment response (e.g., age, sex, baseline fatigue severity, autonomic function). Linear or logistic regression models will be employed, including interaction terms where appropriate. These analyses are hypothesis-generating; results will be interpreted cautiously and without correction for multiplicity, and effect sizes with 95% CIs will be provided. If substantial missing data is observed, multiple imputation will be undertaken as a sensitivity analysis. Consistent with the intention-to-treat principle, all randomized participants will be included in primary analyses; while the per-protocol analysis will be restricted to those attending ≥ 70% of sessions. Adherence rates may be incorporated as covariates in exploratory models.

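### Randomisation is restricted by wave and by strata, but the mixed model contains neither; if those factors are prognostic, the test of the 12-week difference is needlessly conservative

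*Protocol article*

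**What the plan says.** Section 2.8 sets out the allocation. "Recruitment will occur in three waves (*n* = 50, 49, and 48") gives the wave sizes, and the waves are "each randomized independently to ensure a 1:1:1 ratio (16–17 participants per arm per wave"). The sequences are generated in R "using stratified lists to minimize imbalance across groups". The article does not name the stratification factors; it refers to the R script in Supplementary File S1, which is not part of the text at hand.

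Section 2.14 gives the terms of the primary model: "fixed effects for group, time, and their interaction (group × time), and random intercepts to account for within-subject correlation". It applies the same framework to the secondary continuous outcomes. Covariates appear only in the part on categorical outcomes: "Where adjustment for covariates is warranted (e.g., age, sex, baseline fatigue severity), logistic regression analysis will be performed". The Additional Analyses part of 2.14 adds exploratory work on "potential moderators and predictors of treatment response (e.g., age, sex, baseline fatigue severity, autonomic function"). None of these places brings wave or the stratification factors into the primary analysis.

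**The concern.** Restricting the randomisation by a factor makes the arms more alike on that factor than chance would. The group difference then varies less from one possible allocation to the next. A model without the factor does not know this: it leaves the factor's variance in the error term and reports a standard error that is too wide for the design actually used. The usual rule is therefore to analyse by the factors used to randomise.

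Wave could plausibly matter here. Section 5 gives a recruitment period from 1 July 2025 to the end of January 2026, and section 2.11.4 has participants record infections, reinfections and vaccinations as relevant to health. Such influences could differ between waves, although the article gives no wave dates. At stake are some precision and some power on the primary comparison, which could be had at almost no cost.

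**Working it through.** **1. The plan's own figures.** Inputs from section 2.7: difference 6, variance 56.5 (SD = √56.5 = 7.52), one-sided α 0.05, power 80%, design effect 2, dropout 20%.

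- n per arm = 2 × 56.5 × (1.645 + 0.842)² / 6² = 19.41
- 19.41 × 2 / 0.80 = 48.5, rounded up to 49 per arm, 147 in total. The stated size reproduces.
- Waves: 50 + 49 + 48 = 147, which fits 16–17 per arm per wave.

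**2. Effect of leaving balanced factors out.** Let R² be the share of 12-week CFQ-14 variance explained by wave and the strata together. The documents do not give it, so it is an assumption, taken from 0 to 20%. With n per arm and the factors balanced across arms:

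- standard error the model reports: SD × √(2/n)
- true standard error: SD × √(2(1 − R²)/n)
- ratio: 1/√(1 − R²)
- actual two-sided type I error: 2 × [1 − Φ(1.96 × ratio)]

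Power uses the two-sided 5% level of section 2.14 and a difference of 6. Without adjustment it is Φ((6 − 1.96 × reported SE)/true SE). With adjustment it is Φ(6/true SE − 1.96). After 20% dropout n = 49 × 0.80 = 39.2 per arm, so the reported SE is 7.52 × √(2/39.2) = 1.70. Carrying the design effect of 2 into the analysis gives an effective n of 39.2/2 = 19.6 and a reported SE of 2.40.

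| Assumed R² | SE too large by | Type I error | Power, n = 19.6 (without → with) | Power, n = 39.2 (without → with) |
|---|---|---|---|---|
| 0 | 0% | 0.050 | 70.5 → 70.5% | 94.2 → 94.2% |
| 2% | 1.0% | 0.048 | 70.7 → 71.4% | 94.4 → 94.6% |
| 5% | 2.6% | 0.044 | 71.0 → 72.7% | 94.7 → 95.2% |
| 10% | 5.4% | 0.039 | 71.5 → 75.0% | 95.1 → 96.1% |
| 20% | 11.8% | 0.028 | 72.7 → 79.8% | 96.1 → 97.7% |

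The row for 10% with n = 19.6 in full: true SE = 2.401 × √0.90 = 2.278. Without adjustment, (6 − 1.96 × 2.401)/2.278 = 0.568 and Φ = 0.715. With adjustment, 6/2.278 − 1.96 = 0.674 and Φ = 0.750.

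**3. Which contrast is tested.** The formula in step 2 is for the group difference at 12 weeks. A simulation compared this with the change from baseline to 12 weeks. It used complete data, 36 per arm, 6 strata and 3,000 runs per setting. The within-person correlation, after removing the factor effects, was 0.5. The 12-week score and the change score were each analysed by linear regression.

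- Factors explain 20%, with the same effect at both visits. For the 12-week difference, the average model SE was 1.77 without the factors and 1.58 with them, and the type I error was 0.031 and 0.050. For the change contrast, the SE was 1.58 either way, because a constant effect cancels.
- Factors explain 10% constantly and another 10% at 12 weeks only. For the change contrast, the SE was 1.68 without the factors and 1.58 with them. Part of the loss comes back when the factors also affect change.

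**The case against.** The strongest reply is that the loss is conditional and may be small. It is zero if wave and the strata do not predict fatigue, every R² above is assumed, and the strata cannot be judged without Supplementary File S1. Section 2.14 also plans a repeated-measures model with a group × time term. If the decision rests on the baseline-to-12-week change, factors with a constant effect drop out and nothing is lost. All of this stands and limits the size of the point. It does not remove the point, because the stated primary outcome is the 12-week score, and wave effects that arise during treatment do not cancel.

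It may also be said that model detail belongs in an analysis plan. Here, however, the article lists the model's terms, so the model as stated does not match the allocation as stated. Wave alone, which is certain from section 2.8, is enough to show this.

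A reader might infer three stronger things that the documents do not support:

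- *That the primary result would be biased or prone to false positives.* The error runs the other way: intervals are too wide and the type I error is below nominal.
- *That adjustment at R² 10% lifts power from 70% to 75%.* When the factors are balanced by design, the unadjusted test already benefits from a smaller true standard error. It therefore starts at 71.5%, and that figure itself depends on carrying over a design effect that section 2.7 attributes to convenience sampling.
- *That leaving out diagnosis (ME/CFS or PCS) is the same mismatch.* The article does not say that diagnosis is a randomisation factor. The moderators under Additional Analyses are given as examples, so an analysis by diagnosis is not ruled out; it is only not named.

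**Conclusion.** The mismatch between sections 2.8 and 2.14 is real and modest. For the 12-week difference, the model-based standard error is between 0 and about 12% too large and the two-sided type I error lies between 0.050 and 0.028, for an assumed R² from 0 to 20%. The power gained by adjusting at R² 10% is about 3.5 percentage points with the design effect of 2 (75.0 − 71.5) and 1 point without it (96.1 − 95.1). These figures rest on balance of the factors across arms, on the plan's variance of 56.5 and difference of 6, and on the test being of the 12-week score. For the change contrast, precision is lost only if the factors also affect change. The change is worth making because it is nearly free, not because the trial's conclusion is endangered.

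**What to change.** In section 2.14, state that the primary and secondary mixed models include wave (3 levels) and every factor used in the stratified lists of Supplementary File S1 as pre-specified fixed effects, each with its interaction with time. The interactions are needed because main effects alone do nothing for influences that differ between visits.

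The cost is a few degrees of freedom. For wave with three measurement times it is 2 for the main effect and 2 × 2 = 4 for the interaction; the strata add to this according to their number of levels. Wave and stratum are known at randomisation, so no new data are needed, and the sample size stays at 147. Recruitment is described as ongoing, so the wording should be fixed before any unblinded look at the outcome data.

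As a secondary suggestion, diagnosis could be added as a covariate and diagnosis × group named among the exploratory moderators, reported as an estimate with a 95% confidence interval. This is optional, for the reason given under the objection.

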### 2.6. Recruitment

Recruitment will be conducted in collaboration with REiCOP and affiliated patient associations. These organizations will disseminate information about the study aims, eligibility criteria, and contact details for the research team. A call for participation will also be posted on social media. Interested individuals will contact the research team to receive an information sheet and schedule a first online meeting with the lead researcher, during which a brief structured interview will verify eligibility and provide detailed information on study procedures.

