## 5. Trial Status

The trial is ongoing and is currently during the recruitment phase. Recruitment was initiated on 1 July 2025, and is expected to be completed by the end of January 2026. 

Protocol version 4 (29 September 2025). The trial was registered at ClinicalTrials.gov (NCT06978582) on 15 May 2025, and the most recent update was posted on 29 September 2025. 

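### A seeded randomization script is cited as a supplement while recruitment is open; if it shows the live seed, sealed envelopes do not conceal the assignments still to come

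*Protocol article*

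**What the plan says.** Section 2.8 describes how the lists are made: "Randomization sequences will be computer-generated in R (with seed set for reproducibility) using stratified lists to minimize imbalance across groups". The next sentence says where the code is: "The R script for the stratified randomization is in Supplementary File S1". Recruitment runs in three waves of 50, 49 and 48, each randomized separately at 1:1:1.

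For concealment the same section relies on envelopes: "Allocation concealment will be ensured with sequentially numbered, opaque, sealed envelopes, prepared by an independent collaborator not involved in recruitment or assessment". On timing it says: "Envelopes will be opened only after consent and completion of baseline assessments".

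Section 5 gives the trial's status: "The trial is ongoing and is currently during the recruitment phase". It continues: "Recruitment was initiated on 1 July 2025, and is expected to be completed by the end of January 2026".

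Section 2.6 has the lead researcher hold a first online meeting with each candidate, "during which a brief structured interview will verify eligibility and provide detailed information on study procedures".

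The Data Availability statement says, in the future tense, that study materials will accompany the article that reports the trial. It carries a repository access date of 12 October 2025, which falls within the planned recruitment period.

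**The concern.** Sealed envelopes protect an assignment only if it cannot be learned in another way. A generator run from a known seed gives the same list each time. The article says that the seed is set so that the lists can be reproduced, and it points to a supplement for the script during enrolment. It mentions no embargo on the script and no masking of the seed. The independent collaborator's stated task is to prepare the envelopes. The text does not say who generates the sequence or who holds the seed.

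Concealment carries much weight in this trial. Section 2.9 accepts that participants and therapists are unblinded, and the primary outcome in section 2.11.1 is a self-reported fatigue score. Some eligibility decisions involve judgement: section 2.4 requires no prior formal diagnosis, and section 2.3 excludes people unwilling to make small changes to daily habits. A recruiter who could see the next assignment would have room to influence who enters which arm. Once a participant has been enrolled with the assignment foreseeable, that cannot be undone in the analysis.

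**Working it through.** **Inputs.** Wave sizes 50, 49 and 48, 1:1:1 allocation, the seeded R script and its location come from section 2.8. The total of 147 (49 per group) comes from section 2.7. Recruitment status and dates come from section 5.

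**The plan's own figure.** 50 + 49 + 48 = 147. Splits of 17/17/16, 16/16/17 and 16/16/16 give each arm 49 (17 + 16 + 16 for the first two, 16 + 17 + 16 for the third). The wave plan agrees with the sample size.

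**Predictability with the seed.** A 48-place list with 16 per arm was generated twice from one seed, and the two lists were identical. A list from a different seed matched it in 18.75% of positions (9 of 48). The check was run in Python; the same principle applies to a seeded generator in R. Someone who holds the live seed, the wave sizes, the strata and the order of entry can therefore predict 100% of the remaining assignments.

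**Predictability without the seed.** Assume one permuted list per wave, known arm totals, all earlier assignments known and no strata. The best strategy is to guess the arm with most places left. In 20,000 simulated lists for each wave, this was right in 43.3% (17/17/16), 43.5% (16/16/17) and 43.4% (16/16/16) of assignments. Blind guessing is right in 1/3 = 33%. Code without the seed does not reveal the sequence, although it would show any block structure.

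**Share of the trial at risk.** The article does not say how many waves had been allocated when S1 became available, so only a range can be given:

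| Situation (assumed) | Exposed | Share of 147 |
|---|---|---|
| Live seed not in S1, or later waves use other undisclosed seeds | 0 | 0% |
| Live seed and inputs in S1, third wave remaining | 48 | 48/147 = 32.7% |
| Live seed and inputs in S1, second and third waves remaining | 49 + 48 = 97 | 97/147 = 66.0% |

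**Passages side by side.** Section 2.8 says in the present tense that the script is in S1. The Data Availability statement says that materials will come with the article reporting the trial. If that means the results article, the two disagree on when the script is released. If it means this protocol article, release falls at a time when the text describes recruitment as open.

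**The case against.** The strongest reply is that the deciding fact is in a file not shown. A script can be published with the seed masked, and section 2.8 does not say that the seed is printed in S1. Each wave is randomized separately, so later waves may use other seeds or lists that did not yet exist. An assignment also depends on stratum and order of entry, and if a wave is randomized as a batch, there is no next assignment to foresee at the eligibility interview. No publication date is given for S1. The stated safeguards are standard: an independent preparer, opaque numbered envelopes, and opening only after consent and baseline. Section 2.4 further limits discretion by requiring documentation of a prior medical evaluation and a structured check of records.

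Most of this stands. A reader might infer that the remaining sequence can in fact be regenerated and that the envelopes have already failed. The documents do not support that, because it needs the live seed and all inputs to be in S1 for waves still unallocated. A reader might also want the bias expressed in fatigue points. The documents give no basis for the size of any steering effect, so no such figure is offered.

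What does not stand is that the envelopes answer the point. They guard against reading an assignment early, not against recomputing it. Nothing in the article says that the seed is withheld or that it differs between waves.

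**Conclusion.** The point holds in conditional form. The article combines three statements: a seed set for reproducibility, a script cited as a supplement, and open recruitment. Together they are a real threat to concealment that sealed envelopes cannot repair. If S1 shows the live seed and inputs for any unallocated wave, those assignments are fully predictable instead of about 43% guessable. That would affect 33% of participants with one wave remaining, or 66% with two. If the live seed was never disclosed in S1 or to recruiters, this exposure is absent.

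The conclusion assumes nothing about S1 beyond its description as holding the script, and it does not claim that any assignment was foreseen. The 43% rests on the simple list structure stated in the working; strata or smaller blocks would change it. The threat is serious enough to act on because participants and therapists are unblinded, the primary outcome is self-reported, and loss of concealment cannot be corrected after enrolment.

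**What to change.** 1. Establish whether the live seed appears in S1 or has been available to anyone who recruits participants.
2. Unless it is confirmed that it was not, have the independent collaborator draw new lists for every wave or participant not yet allocated. The fresh seed should be withheld from recruiters, assessors and the public, and the envelopes resealed.
3. Until the last allocation, keep only a seed-free template of the script public. Release the seed and the executable script afterwards.
4. Reconcile section 2.8 with the Data Availability statement on when the script is released.

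The cost is about an hour of the collaborator's time and a short amendment. Full reproducibility is delayed until allocation ends, but not lost. Assignments already made are unaffected.
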